### Wii.n.Walk Intervention

Participants in the experimental group will receive the Wii.n.Walk intervention. The Wii.n.Walk intervention was developed by core members of the research team and refined based on observations and the feedback received from the participants in the pilot studies [30]. Modifications for trainer instructions were made to Wii Fit postures and activities to prevent incorrect postures/techniques and to promote function and safety. Preliminary work also informed the dosage/frequency and duration of the intervention.

Social Cognitive Theory (SCT) [36] is the theoretical foundation for the Wii.n.Walk intervention. This theory was developed to enhance all four sources of self-efficacy: performance mastery, vicarious learning, verbal persuasion, and reinterpretation of physiological responses. Performance mastery, or learning to perform a specific skill, is the most robust source of self-efficacy. Successful performance of the Wii.n.Walk activities may provide a sense of accomplishment and thereby improve self-efficacy. Vicarious learning, or learning by watching others successfully accomplish activities, provides the observer a sense that they, too, have the ability to accomplish the task. This will be established by performing the Wii.n.Walk activities in groups initially and having participants watch the other group members perform the activities. Verbal persuasion will arise from credible feedback, guiding the learner through the task, and motivating his or her best effort. The trainer will provide this feedback when appropriate—at least once each session for each group member. The Nintendo device also automatically provides auditory and visual feedback based on the participant’s performance. Finally, participants will be taught to reinterpret physiological responses (eg, stress and anxiety) that may be associated with challenging Wii.n.Walk activities. According to a systematic review, physical activity programs that incorporate SCT are more effective in enhancing adherence [37]. More specifically, social support, peer modeling, and group training have been identified as important factors for increasing adherence in older adults [38].

The Wii.n.Walk protocol consists of Wii Fit activities. Participants stand on the Wii Fit balance board and play the games through weight shifting or by using the Wii remote control. The intervention protocol includes selected activities and exercises including yoga (static and dynamic single and double leg poses), balance tasks (lateral, posterior, and anterior weight shifting exercises), strength training (dynamic single and double leg exercises), and aerobics (running on the spot and step class).

Participants will complete two training phases: a 4-week supervised phase (3 times/week, 40 minutes training /session) followed by a 4-week unsupervised phase. Based on our pilot studies, completion of 40-minute Wii Fit exercises in each session takes approximately 60-90 minutes for the participants, including the instructions given by the Nintendo software as well as the rests that may be needed between the exercises. Participants will meet in groups of three at their local rehabilitation center with an experienced trainer during the first week to learn the program. They will then complete the final 3 weeks of the supervised program at home while being remotely supervised by the trainer and remotely interacting with the other two group participants. During the supervised phase, the trainer will provide individualized intervention and advance the training as the participant improves. At the end of the 4-week supervised phase, participants will retain the Wii units and be encouraged to use the program on their own for an additional 4 weeks (unsupervised phase).

The supervised phase purposely begins with in-person visits to introduce participants to the program, initiate group dynamics (eg, peer support), and create familiarity with the activities in a monitored safe environment. Graduating to home sessions overcomes barriers, cost, and inconveniences associated with travelling to a rehabilitation clinic and is intended to reinforce continued participation [22]. Supervised phase home sessions will be monitored by a trainer remotely using iPads with Wi-Fi plus cellular (Apple Inc, Cupertino, California, USA), preloaded with the VidyoMobile videoconferencing application (Vidyo Inc, Hackensack, New Jersey, USA). VidyoMobile enables the participant to meet at home with the trainer and the other two participants in the group. For better sound quality, participants will be asked to wear wireless headphones (Kinivo, Bellevue, Washington USA) with noise cancellation features. The iPad interface has been simplified as much as possible. Only the VidyoMobile app is available to the participants (access to all other apps is disabled through the iPad’s parental control feature), and they can connect to the trainer by entering only their names and a simple PIN code. iPads will be securely mounted on a sturdy tablet tripod and will be placed a few meters away from the participant’s TV and behind the participant, so that the trainer can see both the participant’s screen as well as his or her posture. The ideal location will be established by the trainer during the home setup of the Wii.n.Walk equipment. At the beginning of each session, the trainer will hold a brief discussion session with all participants, through the videoconferencing software, to review the plan for the session and address any questions. Once the session begins, the trainer is able to watch and supervise all three participants from his or her desktop/laptop at the clinic. The participant’s iPad can display the trainer and the other two participants. The trainer can remotely deactivate each iPad’s camera to reduce distractions while exercising or to reduce video streaming costs. The trainer will activate the iPad’s camera on at least two occasions during each session to enable opportunities for vicarious learning and participant-to-participant verbal persuasion. As an example, the trainer will ask two participants to watch the third perform an exercise. Verbal persuasion will be provided by the trainer to the participant being watched.

The exercises/games and their difficulty levels will be chosen by the trainer. The three participants in the same group will perform similar sets of exercises/games; however, the difficulty level of the exercises/games will vary depending on each participant’s abilities. By default, the more challenging levels of the games are initially locked and can only be unlocked if the participant successfully completes easier, prerequisite levels. In addition, progression to more difficult and longer activities is guided by instructions in the Wii.n.Walk manual. The manual also provides modified activity positions such as adding unilateral or bilateral external hand support if required by the participant. Modifications can be made if the participant has difficulty or is unable to do the activity. As an example, activities may be modified for an individual with a TF amputation if the prosthesis is not structurally capable of assuming the exercise position (eg, some of the exercises require stance phase prosthetic knee flexion). Common postural mistakes are included in the manual to guide the trainer in correcting positioning.

At the end of the supervised phase, the iPads, stands, and headphones will be collected by the trainer, while participants will retain the Wii console and balance board for the unsupervised phase. Participants will be encouraged to use the Wii.n.Walk program as much as they like during the unsupervised phase by continuing to do the same exercises/games they did during the supervised phase and progressing to the challenging levels if they unlocked those levels*.* To avoid confounding information, other people living with the participant will be asked not to use it. The trainer will telephone the participant once a week to monitor for safety (eg, falls) and equipment function.

For both supervised and unsupervised phases, depending on the level of ability and potential for safety issues, participants will be asked to have two high-back chairs placed on either side of them to minimize the risk of falling while using the Wii.n.Walk program. For participants who require additional assistance, if available, a family member, friend, or caregiver will be encouraged to be present during the training sessions. As the participant’s abilities improve, they will progress from the use of such assistance.

### Control Intervention

The control group will follow the same protocol but will be trained to use the Wii Big Brain Academy Degree program (Nintendo, Kyoto, Japan). Big Brain is a low-cost, commercially available software consisting of video games to improve cognitive function. Participants will use the Wii remote to participate in the games by pointing and clicking to select answers in response to on-screen questions. Big Brain games require participants to identify, memorize, analyze, compute, and visualize. The games have easy, medium, and difficult levels. Participants initially start with easy games and progress to more challenging levels based on their performance. The trainer will design the supervised sessions, provide instruction/feedback, and facilitate group discussions. Results from the feasibility study indicate that participants enjoyed discussion about topics including which games are harder, strategies for doing better at different games, and comparing scores.

We chose cognitive video gaming for the control intervention because (1) it enables non-specific attention control, (2) there is minimal concern that it will impact the primary outcome because of its non-physical nature, (3) it uses similar technology as Wii.n.Walk, (4) our feasibility data suggest that it maintains motivation and therefore decreases attrition, and (5) it is potentially beneficial and ethically acceptable [39]. Two separate trainers will administer the Wii.n.Walk and control interventions to minimize treatment bias.

### Outcome Evaluation

#### Overview

Outcomes will be evaluated (Figure 1) by blinded evaluators at baseline, end of the supervised phase (week 5), end of the unsupervised phase (week 10), and end of retention period (week 62). The evaluators will be senior university students in health sciences and will have at least 1 year of experience working with research participants. They will be trained by co-investigator, BI, who has more than 5 years of experience working with amputees and administering the outcome measures used in this study.

#### Primary Outcome Measure

The Two-Minute Walk Test (2MWT) will be used to measure walking capacity as the primary outcome measure. Starting from a standing position, participants will be asked to walk as far as they can in a safe manner for 2 minutes over an indoor, flat, out-and-back course. The distance travelled to the nearest meter is recorded. The Canadian Physical Medicine and Rehabilitation Association’s Amputee Special Interest Group [40], and others [41,42], have recommended the 2MWT as the preferred measure of walking capacity. It is used in more trials of individuals with LLA [43-53] than any other measure, enabling us to compare our results with previous studies. The 2MWT has been validated with a number of LLA samples [41,42,51-53]. The 2MWT has demonstrated intra-rater reliability (intraclass correlation coefficient/ICC=.96), inter-rater reliability (ICC=.98) [51], and validity and responsiveness to change (mean 13.6, SD 19.9 meters) in individuals with LLA [52].

#### Secondary Outcome Measures

The Short Physical Performance Battery (SPPB) will capture timed standing balance (parallel foot stance, semi-tandem, or tandem: 10 seconds each), lower limb strength captured using time (to the nearest second) taken to complete five sit-to-stand chair transfers (no hand support), and gait speed (to the nearest second) over 4 meters using a standing start [54]. There is support for test-retest reliability (ICC=.92) and validity in older adults with disability [55,56]. Due to observing a ceiling effect for this measure in our earlier pilot work, we modified the scoring of the scale by timing each of the standing balance tasks for up to 30 seconds. An additional item, timed single leg stance (up to 30 seconds for each leg), was added to evaluate single leg stance balance.

The Four Square Step Test (FSST) will be used to measure dynamic standing balance. Electric tape is used to create four squares on the floor [57]. The participant is asked to step in each square, first clockwise and then counter-clockwise, without touching the tape, as fast as possible, and with use of his or her walking aid if needed. This test is timed and faster times indicate better dynamic standing balance. Scores ≥24 seconds indicate the individual is at risk for falls [58]. FSST has shown to be reliable (ICC=.98) and valid in older adults [57].

The Physical Activity Scale for the Elderly (PASE) is a self-report measure that captures information on the frequency, duration, and intensity of various physical activities [59]. The 10-item PASE has two parts: Part 1, Leisure Time Activity, has six items about involvement in daily activities such as participating in light exercise during the past 7 days. The response options are “never”, “seldom”, “sometimes”, or “often”. Information on the type and the mean time spent engaging in the activity per day is also captured. Part 2, Household Activity, has three “yes/no” items about participation in daily activities. The last question asks about number of hours per week, as well as the amount of physical activity involved, in paid or volunteer work. The amount of time spent and participation (yes/no) are multiplied by a weighted value. The total PASE score is derived by summing each contribution and varies from 0 to 500, with higher scores representing higher physical activity levels. Test-retest reliability (ICC=.84) and validity have been reported for older adults [59].

The Activities-specific Balance Confidence (ABC) is a 16-item self-report scale to assess perceived balance confidence [60]. The item scores are summed and divided by 16 to derive a mean overall score varying from 0 to 100, with higher scores indicating more confidence. Validity and test-retest reliability (ICC=.91) have been shown in individuals with LLA [61].

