The Walking While Talking Test (WWT) is a test of divided attention to examine cognitive-motor interactions [69-72]. The WWT requires the ability to divide and switch attention between two tasks, and it has been reported that older adults show an innate preference for preserving gait over talking [73,74]. Participants walk 6 meters on a flat course, turn around, and walk 6 meters back to the start while reciting the letters of the alphabet (a, b, c, ...) aloud (WWT-simple). They repeat this routine while reciting alternate letters of the alphabet (a, c, e, …) aloud (WWT-complex). The difference in time (to the nearest second) to complete the simple and complex walks will be calculated with higher differences suggesting poorer ability to cope with dual tasks (eg, greater need to focus on walking). Inter-rater reliability (*r*=.602) and validity have been reported in older individuals [75]. The WWT will be collected with the goal of “misdirecting” participants and masking the study objectives.

The Fall Calendar will be used to document the number of falls, circumstances (eg, cause, location, assistive device used or not), and consequences participant have had (eg, medical visit, injury) over the course of study.

Adherence will be measured by total amount of the program use (minutes, frequency, and duration), which will be collected from the Wii console at the time of equipment pick-up.

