### Sample Size Calculation

The primary outcome (2MWT) was used to calculate the sample size. The responsiveness of the 2MWT in a single study that included older adults with LLA being discharged from rehabilitation had a mean of 13.6 (SD 19.9) meters [52]. In an RCT of younger (mean age 36 years) community-dwelling individuals with LLA, the mean difference between treatment and control groups was 11.2 (SD 18.4) meters [43]. Walking distance gains from our own pilot work (mean 25, SD 18.1 meters) on younger adults in rehabilitation [30], and early results from our feasibility study (mean 11.9, SD 9.3 meters) using a similar sample as the proposed study, suggests distances of up to 14 meter gains may be possible. Taking into account these data and based on our study team’s considerable clinical expertise, we decided that the minimal clinically important difference of 14 meters would be reasonable. Using the sample size calculation formula for ANCOVA in RCTs (α=.05; β=.1; rho=.72) [82], each group would require 21 participants. Borm et al [83] demonstrate that when rho lies between .2 and .8, ANCOVA further reduces the required sample size by 10-40% over change score. Accounting for an additional 4 degrees of freedom (one stratification factor for site at randomization and possibly three at analysis), an extra four participants per group (n=25) are required. Accounting for a conservative total group dropout rate of 25% and supported by physical activity clinical trials (8-24%) [84,85], 64 participants are required. Because the supervised sessions are conducted in groups of three, the sample size needs to be divisible by three. Therefore, a final n=72 will allow us to enroll a balanced n of 18 Wii.n.Walk and 18 controls at each site.

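### Timing the 4-meter walk to whole seconds adds avoidable noise to gait speed, a named part of the secondary hypothesis

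*Protocol article*

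**What the plan says.** Under Secondary Outcome Measures, the Short Physical Performance Battery (SPPB) includes "gait speed (to the nearest second) over 4 meters using a standing start". The same sentence sets the same resolution for the chair-stand item: "time (to the nearest second) taken to complete five sit-to-stand chair transfers". Under Tertiary Outcome Measures, the Walking While Talking Test (WWT) is handled similarly: "The difference in time (to the nearest second) to complete the simple and complex walks will be calculated". No timing resolution is stated for the Four Square Step Test.

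The Introduction names gait speed, with balance and strength, as part of the lower-limb functioning that the secondary hypothesis expects to improve. Secondary and tertiary outcomes are compared between groups by ANCOVA with an adjusted F statistic (Secondary/Tertiary Analyses).

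The only quantified walking target belongs to the primary outcome, the Two-Minute Walk Test (2MWT): "we decided that the minimal clinically important difference of 14 meters would be reasonable" (Sample Size Calculation). That test is recorded to the nearest meter (Primary Outcome Measure).

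**The concern.** A 4 m walk takes only a few seconds, so whole-second timing reduces gait speed to a handful of values: 3, 4, 5 and 6 s become 1.33, 1.00, 0.80 and 0.67 m/s. A real change in speed may leave the recorded time unchanged or move it by a full step.

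The article fixes this as a measurement rule. It is not a detail left to an analysis plan, and no later analysis can recover decimals that were never written down. What is at stake is the precision of one secondary outcome in a trial of 72 people that allows for 25% dropout.

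**Working it through.** **Inputs from the article.** Timing unit 1 s and course 4 m (Secondary Outcome Measures). 2MWT target 14 m, "α=.05; β=.1; rho=.72", 72 randomised 1:1 and 25% dropout (Sample Size Calculation; Trial Design).

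**Inputs assumed.** The article gives no baseline gait speed, so I use means of 0.6 to 1.1 m/s and SDs of 0.15 to 0.25 m/s. Applying the 2MWT target to the 4 m walk is also an assumption.

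**The plan's own figure.** n per arm = 2 × [SD × (1.960 + 1.282) / 14]² × (1 − 0.72²). The article does not say which SD it used. With the discharge study's figure ("had a mean of 13.6 (SD 19.9) meters"), n = 20.4, rounded up to 21, which matches the article. SD 18.4 gives 17.5 and SD 18.1 gives 16.9. So 21 is reproduced with SD 19.9, two-sided α and ρ = 0.72, and I keep that α and ρ below. Analysed size per arm: 36 × 0.75 = 27.

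**Width of a recorded value.**
- 4 s: 4/4.5 = 0.89 to 4/3.5 = 1.14 m/s
- 5 s: 4/5.5 = 0.73 to 4/4.5 = 0.89 m/s
- For comparison, 1 m on the 2MWT is 1/120 = 0.008 m/s.

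**Target-sized gain on the 4 m course.** 14/120 = 0.117 m/s. Time saved = 4/v − 4/(v + 0.117): 1.09 s at v = 0.6, 0.64 s at 0.8, 0.42 s at 1.0 and 0.35 s at 1.1 m/s. It is less than one recording unit above about 0.63 m/s (0.63 × 120 ≈ 75 m in two minutes).

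**Individuals.** The same true gain of 0.117 m/s can be lost or overstated:

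| True speed (m/s) | True time (s) | Recorded (s) | Recorded gain (m/s) |
|---|---|---|---|
| 0.80 → 0.917 | 5.00 → 4.36 | 5 → 4 | 0.20 |
| 1.00 → 1.117 | 4.00 → 3.58 | 4 → 4 | 0 |
| 1.10 → 1.217 | 3.64 → 3.29 | 4 → 3 | 0.33 |

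**Group comparison, by hand at 1.0 m/s, SD 0.20.** Rounding error in time has SD 1/√12 = 0.289 s. In speed this is about (v²/4) × 0.289 = 0.072 m/s.
- Exact times: residual variance 0.04 × (1 − 0.72²) = 0.0193; SE = √(2 × 0.0193/27) = 0.0378; 0.117/0.0378 = 3.09; power Φ(3.09 − 1.96) ≈ 87%.
- Rounded times: variance 0.04 + 0.072² = 0.0452; correlation 0.0288/0.0452 = 0.637; residual variance 0.0452 × (1 − 0.637²) = 0.0269; SE = 0.0446; 0.117/0.0446 = 2.62; power ≈ 74%.

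This understates the loss, because the noise grows with v² and faster walkers carry more of it than the mean does.

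**Group comparison, by simulation.** ANCOVA on speed, 27 per arm, ρ = 0.72, true difference 0.117 m/s, SD 0.20 m/s:

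| Mean speed (m/s) | Exact time | Whole seconds |
|---|---|---|
| 0.6 | about 85% | 82% |
| 0.8 | about 85% | 77% |
| 1.0 | about 85% | 68% |
| 1.1 | about 85% | 62% |

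Independent runs agree to within a few points. The estimated mean difference with whole seconds stays at about 0.11 to 0.125 m/s against the true 0.117. The SD also matters: at mean 1.0, power falls from 98% to 85% with SD 0.15 and from 68% to 55% with SD 0.25. If time rather than speed is analysed, the loss at mean 0.8, SD 0.20 is smaller (76% to 72%).

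**Chair stand.** Rounding inflates the required n by 1 + (1/12)/SD²: about 2% for an assumed SD of 2 s and 0.3% for 5 s.

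**WWT.** If both walks are rounded, the factor is 1 + (2/12)/SD²: about 4% for an assumed SD of the difference of 2 s and 1% for 4 s, rising to 17% only at 1 s. If only the difference is rounded, these are halved. On the 12 m course a 0.117 m/s gain changes one walk by 1.9 s at 0.8 m/s and 1.3 s at 1.0 m/s, more than one unit.

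**The case against.** A reader might infer that whole-second timing makes these tests too coarse to detect the gain the trial is after, or that it biases the result toward no change. The article does not support either. It plans to compare group means by ANCOVA, and rounding leaves the mean difference nearly intact; what falls is power. Missed individual changes are offset by overstated ones, as the three examples show.

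A reader might also extend the point to every timed test. That fails too. Rounding is negligible for the chair stand and minor for the WWT. The WWT wording can be read as rounding only the difference, the test is collected to disguise the study's aims, and it appears in none of the stated hypotheses. No rounding is stated for the Four Square Step Test, so no fault is shown there.

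Three further objections limit the size of the gait-speed point. The 14 m target belongs to a different walking test, and equal speed gain on both is an assumption. The larger losses need faster walkers; near 0.6 m/s the cost is about 3 points. And the 4 m walk is one item of the SPPB. The article does not say that it is analysed alone as continuous speed, while the primary outcome captures walking far more finely and the sample size does not depend on gait speed.

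All of this stands, and it makes the point minor. It does not justify the rule: gait speed is named in the secondary hypothesis, and whole-second recording has no stated benefit.

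**Conclusion.** The point holds for the 4 m walk only, as a minor and easily avoided loss of precision. Recorded values are 0.16 m/s (5 s) to 0.25 m/s (4 s) wide. Under the stated assumptions, power on gait speed drops from about 85% to between 82% and 62% as mean speed rises from 0.6 to 1.1 m/s, with little bias in the group difference. The bin widths follow from the article alone. The power figures depend on an assumed mean and SD of gait speed and on carrying the 2MWT target over. The primary analysis and the sample size are not affected.

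**What to change.** In the evaluator instructions and on the case report form, record the 4 m walk time to 0.1 s or finer. Compute speed from that unrounded time, and apply any categorical SPPB scoring only afterwards. Recording the chair stand and both WWT walks the same way, and stating a resolution for the Four Square Step Test, would be consistent but is optional.

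The cost is about one line in each document, with no added procedure, visit or staff. The article reports that nobody had yet been enrolled, so at that stage every baseline could still be captured at the finer resolution.
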